### Risks and benefits

No serious side effects or adverse events have been previously reported due to hemp or casein protein intake.

Phlebotomy carries a potential health risk. DXA scans expose participants to x-rays. Participants will be encouraged to report any adverse events as they happen, and participants will be prompted and asked on a weekly basis about adverse events. Adverse events will be recorded through the “Adverse Event/Unanticipated Problems Form” provided by the Research Ethics Board (REB). All serious adverse events will be reported to the University of Manitoba REB which has approved the trial protocol. Study coordinators will follow up with participants via email or telephone after adverse events until symptoms have resolved. If the serious unexpected adverse reaction (SAEs) is fatal or life-threatening, the Therapeutics Products Directorate of Health Canada will be notified no later than 7 days after the sponsor becomes aware of the information. If the serious unexpected adverse reaction is neither fatal nor life-threatening, the Natural and Non-prescription Health Products Directorate (NNHPD) will be notified immediately if possible, and no later 15 days after the sponsor becomes aware of the information. Within 8 days after having informed the NNHPD of a serious unexpected adverse reaction to the NHP, the sponsor will submit a report as complete as possible that includes an assessment of the importance and implication of any findings. The final report will include relevant previous experience with the same or similar health products. The trial will be conducted following the principles of Good Clinical Practice.

### Concomitant therapy

All prescription and over-the-counter medications that are not deemed as falling into the exclusion criteria list will be recorded at the screening visit by a general physician and will be monitored on a weekly basis during the treatment periods. Should a medication be prescribed or started during the trial period, it will require qualified investigator approval.

### Anticipated results and conclusion

It is anticipated that the additional 50 g/day of dietary protein, whether from casein or HSP, or HSP+, will result in a reduction in BP compared to the baseline of the trial. Such results would support a simplified message that increasing dietary protein, by consuming 50 g per day of protein through the use of protein powders, can help lower BP. Such a recommendation is easier to explain and implement than recommendations where a specific macro-nutrient like carbohydrate or fat must be replaced by protein to have anti-hypertensive effects.

It is also anticipated that the hemp protein treatments will lead to a greater reduction in BP compared to the casein, due to their increased arginine concentration. These results will be accompanied by increased blood NO concentrations on the hemp protein treatments. This finding would suggest that HSP, or protein sources with higher arginine, are appropriate choices of protein to select for individuals who may be looking to control their BP rather than lower arginine dietary protein sources.

The HSP+ can be predicted to lead to the greatest reduction in BP. The HSP+ treatment is predicted to demonstrate the greatest reduction in ACE activity due to the ACE-inhibitory effects of the bioactive peptides. If an additional benefit is seen with the addition of HSP bioactive peptide to the HSP, this finding would suggest that dietary protein and bioactive peptides lower BP through separate or synergistic mechanisms, and that a combination of increased dietary protein and bioactive peptides could be recommended for greater BP reduction over and above a simple increase in dietary protein intake.

This proposed trial should directly address gaps in the scientific literature surrounding the anti-hypertensive properties of dietary protein. An increased understanding and demonstration of the anti-hypertensive properties of dietary protein and food-protein-derived bioactive peptides is required before greater recommendations of increased dietary protein can be made to individuals who are looking to control their BP without resorting to pharmaceutical agents.

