## Background

Hypertension afflicts over 7.3 million Canadians [1] and is the number-one modifiable risk factor for death and disability globally [2], accounting for 13.5% of all global premature deaths [3]. Over the last 25 years, treatments to control hypertension have increased markedly in Canada [4]; however, one third of the diagnosed hypertensive population remains uncontrolled and many people remain undiagnosed. Uncontrolled hypertension can lead to a spectrum of diseases including stroke, coronary artery disease, as well as heart and kidney failure [5].

The exact etiology of the development and progression of primary hypertension remains uncertain; however, both genetic and lifestyle factors, including diet in particular, have been implicated. Many interconnected contributing factors have been proposed to explain the increase in blood pressure (BP) leading to hypertension. Factors include over-activation of the renin-angiotensin-aldosterone system (RAAS), endothelial dysfunction, elevated sympathetic activation, and other genetic predispositions [6–8]. Current therapeutic agents for BP control have proven to be reasonably effective; however, the incidence of mortality due to high BP is still on the rise [9]. Consequently, an important need exists for alternative therapeutic strategies to prevent or manage hypertension.

Lifestyle interventions that have been shown to prevent hypertension include maintaining a healthy body weight, taking moderate physical activity, eating a low-sodium diet, reducing alcohol consumption, and adherence to a diet rich in fruit and vegetables [10]. Another emerging potential therapeutic lifestyle strategy to prevent or manage hypertension is increasing dietary protein intake [11, 12]. Both increases in dietary protein intake as a macronutrient [12–16], and as smaller doses as bioactive peptides [17–19], have shown the potential to reduce BP. Indeed, evidence exists that plant-based protein sources may be more effective than animal sources; however, these data stem mainly from observational trials and are inconsistent [11, 20]. Randomized controlled trials comparing plant-based protein sources to animal-based protein sources are limited [12, 21–23]. An essential plant-based protein source that may have anti-hypertensive properties is hemp seed.

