## Methods/design

### Objectives and hypothesis

The aim of this study is to assess the hypotensive potential of consuming whole HSP, and HSP+, compared to casein protein in patients with hypertension. The hypotheses to be tested in this study are as follows: Hypothesis 1: consumption of 50 g/day of dietary protein, of any type (casein, HSP or HSP+) for 6 weeks will lead to reduced 24-h SBP compared to baseline. Hypothesis 2: consumption of 50 g/day of hemp-based dietary protein (HSP and HSP+) for 6 weeks will reduce 24-h SBP compared to casein. Hypothesis 3: consumption of 45 g/day hemp protein with an added 5 g/day of HSP+ for 6 weeks will reduce 24-h SBP compared to 50 g/day of HSP.

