**Fig. 2 Fig2:**
[figure not shown]
Representation of the trial enrollment, interventions and analysis

During each treatment period, participants need to come to the RCFFN twice a week on Tuesdays and Fridays to consume one treatment under supervision and pick up treatments for the next 2 or 3 days. Each treatment consists of a frozen fruit smoothie (mango or pineapple), fruit juice (diet mango juice), sorbet and 25 g of protein from treatment-protein powder and the treatments will be consumed twice a day. HSP and the HSP+ powder has a green color and a stronger taste than casein-protein powder; however, our team has identified that by using a combination of frozen fruit and sorbet in the fruit smoothies this color and taste can be well-masked.

Participants will be instructed to consume two or less alcoholic beverages and no more than three 8-oz. cups of caffeine-containing beverages per day during the trial period. Participants will be instructed to perform their normal daily activities during the measurement day. Prolonged intense physical activity will be discouraged on measurement days and the days preceding measurement days. Participants will be strongly recommended to maintain consistency in their physical activities and dietary pattern during the trial period. A 3-day food record will be collected during the first day of the first phase and during the final week of each treatment period to be analyzed for calorie intake during the study.

During the study period, body weight will be monitored as a change could occur due to the inclusion of extra protein in a free-living condition. All outcome variables will be adjusted for changes in body weight should significant changes occur between treatments. Gastrointestinal tolerability and weekly monitoring questionnaires will be completed by participants weekly during each intervention period.

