### Study groups

Eligible participants will be assigned randomly to one of the following sequences: ABC, ACB, BAC, BCA, CAB or CBA. So, all the participants will be provided with all three treatments in a crossover design.

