### Outcomes and measurement tools

The primary outcome of this trial will be 24-h SBP, measured at the first day of the first phase and day 41 of each treatment phase using ambulatory BP monitors (ABPM, OnTrak, Spacelabs Healthcare Inc., Snoqualmie, WA, USA) [50, 51]. Participants will be fitted with an ABPM to wear for a full day. Continuous and SBP and DBP measured over 24 h will be recorded.

Office-measured BP, pulse-wave velocity and augmentation index will be determined using an automated oscillometric measurement device (Mobil-O-Graph, IEM, Stolberg, Germany) in an office setting at days 1 and 41 of each treatment phase [52, 53]. Office-measured BP will also be measured at day 22 to track the changes at the midpoint of each treatment phase. This measurement will take place in a quiet room while the participant is in a seated position with their arm resting on an arm rest at heart level. Participants will be advised to rest quietly throughout the measurements. Oscillometric measurement will be performed four times at 2-min intervals. The first measurement will be discarded, and the last three measurements will be averaged to determine office-measured BP. The LCD display of the oscillometric measurement device will be covered so that the participant is blinded to the BP values during the measurements. BP results will not be shared with participants until they have completed the trial.

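### Hypothesis 1 is an uncontrolled before-after comparison, so a fall in 24-h SBP from baseline cannot support the planned message that 50 g/day of added protein lowers blood pressure

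*Protocol article*

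**What the plan says.** Under Objectives and hypothesis, Hypothesis 1 is that "50 g/day of dietary protein, of any type (casein, HSP or HSP+) for 6 weeks will lead to reduced 24-h SBP compared to baseline". Hypotheses 2 and 3 compare the hemp treatments with casein, and HSP+ with HSP.

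Under Study groups, "all the participants will be provided with all three treatments in a crossover design". Under Study design (text after Fig. 2), "Each treatment consists of a frozen fruit smoothie (mango or pineapple), fruit juice (diet mango juice), sorbet and 25 g of protein", taken twice a day, so each arm supplies 50 g/day of protein in the same kind of vehicle.

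Under Outcomes and measurement tools, the primary outcome is "24-h SBP, measured at the first day of the first phase and day 41 of each treatment phase". Under Statistical analysis, Dunnett's test takes baseline as the control.

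Two places draw on this comparison. Anticipated results and conclusion says of a fall from baseline on any of the proteins: "Such results would support a simplified message that increasing dietary protein, by consuming 50 g per day of protein" can help lower BP. The last paragraph of the Background lists, as a research gap, the effect of extra protein that does not explicitly replace carbohydrate, and says the design should be able to address the gaps listed.

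**The concern.** Attributing a change to protein needs a comparison in which protein differs and other things do not. Hypothesis 1 has no such comparison. Protein is present at every 24-h reading after the first and absent only at the first, and several other things change at the same point:

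- calendar time;
- the participant's experience of wearing the monitor;
- participation in a supervised trial with twice-weekly visits;
- the fruit, juice and sorbet vehicle;
- possibly regression to the mean, because entry requires SBP of 130 to 160 mmHg.

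None of these can be estimated separately for 24-h SBP. A period term in the model does not help, because no untreated 24-h reading exists after day 1 of phase 1. Adjustment for body weight addresses none of them directly. An analysis plan cannot repair this, since the missing item is a comparator.

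At stake is a general statement about added protein, resting on the primary outcome, that the data could appear to support even if protein had no effect.

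**Working it through.** **1. The plan's own figure.** Sample size gives a difference of 4 mmHg, within-participant SD 5.45 mmHg, power 0.80 and α 0.05 (two-sided assumed). For a paired comparison within participants,

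n = 2 × (1.960 + 0.842)² × 5.45² / 4² = 2 × 7.849 × 29.70 / 16 = 29.1, rounded up to 30.

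This reproduces the stated 30. The exact t calculation gives 32. The arithmetic is not at issue, and the match shows that 5.45 is the SD of a single reading about the participant's own level (SD of a difference √2 × 5.45 = 7.71).

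**2. What the Hypothesis 1 contrast estimates.** Let d be the fall from all non-protein causes that start after the single baseline, and p the fall due to protein. Each arm compared with baseline estimates d + p. Because every later 24-h reading is taken on protein, no contrast estimates d alone.

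**3. What the randomised contrasts estimate.** For arms A and B, (d + p_A) − (d + p_B) = p_A − p_B, so d cancels. Each treatment appears twice in each position across the six sequences, so calendar time is balanced too when the sequences are equally filled.

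**4. Illustration of size.** The article gives no value for d, so d is an assumption and a range is shown. Inputs: n = 30, SD 5.45, p = 0 in every arm, three endpoints sharing one baseline, complete data, two-sided Dunnett critical value c = 2.40.

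- SE of an arm-baseline difference: 5.45 × √(2/30) = 1.407 mmHg.
- Observed fall needed for significance: 2.40 × 1.407 = 3.38 mmHg.
- Given a baseline error z (in units of 5.45/√30 = 0.995), one arm is declared lower with probability q(z) = Φ(z + d/0.995 − 2.40√2). Averaging over z, P(at least one) = E[1 − (1 − q)³] and P(all three) = E[q³].

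| Assumed non-protein fall d (mmHg) | At least one arm significantly lower | All three arms significantly lower |
|---|---|---|
| 0 | about 2% | below 0.1% |
| 2 | about 33% | about 4% |
| 3 | about 64% | about 16% |
| 4 | about 88% | about 43% |

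These treat the SD as known. Estimating it moves each entry by about one percentage point at most. With 35 participants and d = 4 the two figures are about 93% and 54%. The table counts falls only, so the fair null comparison is the first row and not 5%.

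**5. The article's own evidence.** The Background describes a trial in which casein and whey lowered both SBP and DBP against baseline, but mentions only a DBP reduction against the glucose control. It also cites a meta-analysis of controlled trials in which a median of 40 g/day of protein replacing carbohydrate lowered SBP by 1.76 mmHg. The 3.38 mmHg needed in step 4 is 1.9 times that.

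**The case against.** Much can be said for the plan, and part of it stands.

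- **The stated aim is hemp against casein.** That rests on Hypotheses 2 and 3, which are randomised. This stands. A reader might infer that the whole trial is compromised, but the documents do not support that.
- **Some off-treatment data exist.** Office BP is taken on day 1 of every phase, so phases 2 and 3 give readings after a 2-week washout. This is partial information on drift, if the washout is long enough. It does not cover 24-h SBP and cannot isolate the vehicle.
- **The conclusion is hedged.** It is conditional on the results, and the section ends by saying that more evidence is needed before wider recommendations. The Discussion speaks of the real-world effect of drinking protein smoothies. But that describes a package, and the message names protein.
- **All three arms falling is the natural trigger for a message about any protein.** This is fair, so both columns are shown.

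Three stronger readings are tempting and fail. First, a reader might add the trial's limits on alcohol and caffeine as confounders ("instructed to consume two or less alcoholic beverages and no more than three 8-oz. cups of caffeine-containing beverages per day during the trial period"). But entry already excludes more than 14 drinks a week, which equals 2 × 7, and two days without alcohol precede BP measurement. The article attributes no BP effect to the caffeine limit and requires 14 h without coffee before measurement. Nothing shows that alcohol intake falls after baseline. Second, a reader might infer that the Dunnett adjustment takes power from Hypotheses 2 and 3. The article sets p < 0.05 for every analysis and describes no shared alpha or hierarchy. Third, the Background's preventive list includes "reducing alcohol consumption, and adherence to a diet rich in fruit and vegetables". That refers to an overall diet and not to a smoothie with diet juice and sorbet in unstated amounts. The vehicle is a plausible confounder, not one the article itself declares effective.

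**Conclusion.** The concern holds for Hypothesis 1 and for the two statements that depend on it. A fall in 24-h SBP from baseline cannot be attributed to protein. It therefore supports neither the message about 50 g/day nor the claim that the gap on additional protein is addressed. This follows from the design alone and needs no assumption about the size of any drift.

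The size of the risk does rest on assumptions: the drift values, complete data, and the planning SD. Under them, a non-protein fall equal to the 4 mmHg design difference would make at least one ineffective protein look effective in about 88% of trials, and all three in about 43%. Regression to the mean is only a possibility. Selection uses a screening BP while the outcome is a later 24-h recording, so some of it may have passed before baseline.

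Hypotheses 2 and 3 and the sample-size arithmetic are unaffected.

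**What to change.** 1. Report the comparison of each treatment with baseline as a descriptive change, with an estimate and confidence interval, and state that it is not attributed to protein.
2. In Anticipated results and conclusion, withdraw the simplified message or reword it so that it makes no causal claim for added protein.
3. In the last paragraph of the Background, remove the gap on additional protein not replacing carbohydrate from those the design is said to address.
4. State that the trial's conclusions rest on the randomised contrasts in Hypotheses 2 and 3.
5. Name the missing no-protein comparator as a limitation in the Discussion. The day-1 office BP of phases 2 and 3 can be shown as partial information on drift, with its limits stated.

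The cost is wording. No visit, measurement or sample size changes. The investigators give up one causal claim that the design cannot deliver.

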### Participant privacy and confidentiality of data

The following information will be collected during the course of this project: name, address, date of birth, primary telephone number, and sex. This information is recorded (hard copy with scanned electronic back-up copy), which also contains the individual’s written consent to participate in the project. Study records that contain identities will be treated as confidential in accordance with the Personal Health Information Act of Manitoba. These forms will be stored in a locked file cabinet in a locked office in the RCFFN and will never leave the site. The electronic back-ups will be on a single password-protected computer. The contact information will be entered into a separate contact Excel spreadsheet that contains no other personal/health information and will only be used by the study coordinator for the purpose of informing/updating study participants while the study is being carried out. This file is maintained on a single computer and will be password encrypted. The study data will be stored for 25 years after the completion of the study. All paper materials and samples related to the study will be stored in the locked filing cabinet in a locked office or locked freezers at the RCFFN under the supervision of [name]. Only the study coordinators and the principal investigator will have access to the samples. All study documents will bear an assigned participant code. If the results of the trial are published, the identity will remain confidential. All study data will be labeled with only the assigned participant code. This unique code will only be known to the participant and the research study staff. Documents of personal information linking the participants to their codes will be kept separately from any other records, also in a secure locked area. Due to the coding system, there will be no link between personal data and the sample data collected during analysis. All print materials will be destroyed using the contracted document destruction service at the University of Manitoba. All electronic files will be deleted in an encrypted format.

Health Canada may review and research the records for auditing purposes. The University of Manitoba Biomedical REB may review research-related records for quality assurance purposes. Organizations that may also inspect/copy the research records for quality assurance and data analysis include groups such as: Health Canada, their representatives, and other researcher groups who are performing meta-analysis or knowledge synthesis work who request access to the raw data. This review or use of raw data will not include personal information such as name, address, telephone number and/or any other identifying information. Any data required to support the protocol can be supplied on request.

## Discussion

Unlike earlier trials which have compared carbohydrate to protein in terms of BP, the currently proposed trial will compare different types of protein added into the participants’ diet. In this instance, the participant may or may not replace existing calories in the diet with the additional protein. Therefore, the potential exists that increased protein consumption will lead to a change in overall energy intake. An increase in energy intake could occur if the additional calories of the protein are not being compensated for by participants, or a decrease in energy intake could occur due to the satiating properties of protein compared to other macronutrients. These potential shifts in overall energy intake could result in changes in body weight, which could lead to BP changes. Therefore, outcome variables, such as BP, will be adjusted for any significant changes in body weight, which may occur during the treatment periods. Additionally, the mix of fat and carbohydrate being potentially replaced by protein in terms of energy intake may vary between participants. While this trial will not be able to determine exactly whether fat or carbohydrate energy is being replaced with protein, it will reflect the real-world impact of instructing patients and the general public to increase protein consumption by drinking protein smoothies, without specific counseling on replacing other foods.

As in all clinical trials with food-based treatments, potential differences in taste, texture and smell can make the blinding of participants to the treatments difficult. Our research team has worked with HSP and has developed a smoothie recipe which is good at masking the type of protein powder from which it is made. However, if this blinding is not sufficient it may be possible for participants to identify the casein treatment versus the HSP and HSP+ treatments. The likelihood of participants being able to identify the HSP compared to the HSP+ treatment is low. Fortunately given the crossover design and the stringent monitoring of compliance in the proposed trial, it is unlikely that any un-blinding of the participants to the treatments, as described above, would be able to impact the results. All of the outcomes in this trial will be objectively measured; therefore, the impact of knowing if you are on a hemp-based treatment is unlikely to change your outcome measurements.

Knowing you are on a particular treatment, for which your compliance is monitored and controlled, is unlikely to influence your BP measurement, especially given the fact that BP measures will not be shared with participants until they have completed the entire trial.

